**Lay abstract**

How can we reduce the impact of the COVID-19 pandemic on children's mental health? We propose the *Open Sky School*, a nature-based intervention applied in the school setting. Currently, there is increasing enthusiasm for outdoor education in schools, especially since the onset of the COVID-19 pandemic. Could such nature-based interventions have salutogenic effects? Experimental studies conducted worldwide show that contact with nature (e.g., urban park or forest) improves mental health. Preliminary results suggest that this is also the case for children when they come into contact with nature during school hours. However, no experimental studies have tested the benefits of spending time in nature at school as a strategy for improving children's mental health.

To fill the gaps in the existing literature, we will conduct a clustered randomized controlled trial to test the effectiveness of the *Open Sky School* program. The *Open Sky School* is a nature-based intervention applied in the school setting to promote students' and teachers' mental health. The intervention will span 12 weeks, two hours per week. We will recruit 80 to 100 5th and 6th grade elementary school classes from schools in Quebec. The intervention will include mental health promotion activities in and through nature (e.g., cooperation, compassion/empathy, mindfulness) and nature-based educational activities. We will evaluate the effectiveness of this intervention on children's mental health. The results could help decision makers implement education programs involving contact with nature to promote mental health. Our results could provide empirical evidence of such practices that come at little cost and have a high potential for deployment at the population level.

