## 4. Methods

### 4.1. Design

We will implement a clustered randomized controlled trial with a parallel repeated-measures design. In the trial, 80 to 100 schools with 5th and 6th grade classes will be recruited across Quebec and be randomly assigned to one of the following conditions: 1) *Open Sky School* intervention (intervention group) and 2) teaching as usual (waitlist control group, who will receive the intervention the following school year if it is effective). We will randomize at the school level rather than at the class level to allow for more than one class within the same school to take part in the project while avoiding possible contamination effects. In the context of our project we define our nature intervention by exposing children to natural environments during school hours and including any activity that promotes learning or mental health. The available natural space must be located near the school, within a 1 kilometer radius, and can be, for instance, an urban park, wooded area or waterfront. In other words, we are interested in engaging children in nature (in urban or rural areas) and providing access to academic or mental health activities in order to promote their wellbeing.

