### 4.2. Randomization

Randomization will occur after baseline assessments. Once randomization has occurred, it will not be possible to blind researchers and participants within our design. A simple computer algorithm will be used to randomly allocate schools to two parallel and balanced conditions (intervention or control; 1:1 while considering class sizes) by an independent researcher not involved in the study. This will ensure that all schools have an equal opportunity to be allocated into one of the two groups. In the event that multiple teachers from the same school consent to participate, they will be allocated to the same experimental condition to avoid contamination effects.

**Figure 1.** Flow chart of inclusion of participants.

[figure not shown]

Note. a 280 schools in 29 school boards were initially eligible. 4 school boards encompassing 32 schools did not agree to participate and were therefore removed from the recruitment process. b If more than 100 teachers consent to participate, we will randomly select 100 teachers to participate in the trial. c Parents and students must provide informed consent for students to participate in the assessments. Students who do not participate in assessments will still participate in the Open Sky School program. d In the event that multiple teachers from the same school consent to participate, they will be allocated to the same experimental condition to avoid contamination effects. If recruitment targets at the pre-selected school are not met, we will advertise online.

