## **8. Statistical analyses and power**

All analyses will be conducted at the cluster level, i.e., at the school level. Dependent variables will be measured on a continuous scale. Child mental health will be assessed at T1, T2, T3. A longitudinal ANCOVA, as described in Liu et al (2009), will be used to estimate the main and moderating effects described above. The characteristics of the intervention group and the control group will be compared at the class level, where means (e.g., socioeconomic deprivation) could be added to the model as covariates, in the unlikely event that randomization would not have balanced the two groups. A total of 80 to 100 schools (with a minimum of 40 classes if only one class per school participates) will detect small effects (power >90%). An intention-to-treat analysis approach will be used to increase the internal and external validity of the project. The analyses will include any child for whom at least one questionnaire has been completed at least one measurement time and the multiple imputations will be used in case of significant loss to follow-up.

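### The 40-class minimum contradicts 80 to 100 schools unless it is per arm, the size is given in three units, and the >90% power claim is conditional but stated without conditions

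*Protocol*

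**What the plan says.** Section 8 of the protocol gives the whole power statement in one sentence, worded as a total for the trial: "80 to 100 schools (with a minimum of 40 classes if only one class per school participates) will detect small effects (power >90" per cent. The same section makes the school the unit of analysis and names a longitudinal ANCOVA.

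The sample size appears in three units:
- **Classes**, in the lay abstract: "We will recruit 80 to 100 5 th and 6 th grade elementary school classes from schools in Quebec".
- **Schools**, in section 4.1: "In the trial, 80 to 100 schools with 5 th and 6 th grade classes will be recruited across Quebec". Section 8 also counts schools.
- **Teachers**, in note b to Figure 1 (section 4.2): "If more than 100 teachers consent to participate, we will randomly select 100 teachers to participate in the trial".

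Section 4.1 says the trial will "randomize at the school level rather than at the class level", so that more than one class from a school can take part. Section 4.2 places all participating teachers of a school in the same arm.

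**The concern.** The parenthesis "with a minimum of 40 classes if only one class per school participates" does not agree with the number of schools in the same sentence.

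The three units agree only if every school contributes exactly one class, and the design expressly allows more. Precision in this trial depends mainly on the number of schools and on the ICC. A cap drawn on teachers does not protect the number of schools.

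The assurance that the trial "will detect small effects (power >90" per cent) has no stated conditions. If the trial finds no difference, readers will set that result against this promise and may conclude that a small effect has been excluded. Whether they may do so depends on quantities that the sentence does not give.

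**Working it through.** **The plan's own figure.** The >90% cannot be reproduced or refuted. Section 8 gives no numerical effect, alpha, ICC, children per school, baseline correlation or attrition.

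**Step 1: the count.** One class per school gives 80 × 1 = 80 to 100 × 1 = 100 classes. Under 1:1 allocation, 80 / 2 = 40 per arm. Under its own condition, 40 can therefore only be a per-arm number, yet the sentence speaks of a total.

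**Step 2: the units.** With 100 teachers and an average of c classes per school, the number of schools is 100 / c. This gives 100 schools at c = 1, 80 at c = 1.25 and 50 at c = 2. At the cap, any average above 1.25 classes per school leaves fewer than 80 schools.

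**Step 3: power under stated assumptions.**

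From the protocol: K = 80 to 100 schools in total (4.1, 8), 1:1 allocation of schools (4.2), school-level analysis by ANCOVA (8), and a baseline taken before randomisation (4.3).

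Assumed: d = 0.20 SD, two-sided 5%, m = 20 children analysed per school, baseline–outcome correlation r = 0.6 at child and school level, ICC 0.02 to 0.15, no attrition.

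Formulas:
- V = ICC + (1 − ICC)/m
- SE = √[4 × V × (1 − r²)/K]
- Power from the noncentral t distribution with noncentrality d/SE and K − 3 degrees of freedom.

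Example, 80 schools at ICC 0.05: V = 0.05 + 0.95/20 = 0.0975. SE = √(4 × 0.0975 × 0.64/80) = 0.0559. Noncentrality = 0.20/0.0559 = 3.58. Power = 0.94.

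| Schools | ICC 0.02 | ICC 0.05 | ICC 0.10 | ICC 0.15 |
|---|---|---|---|---|
| 80 | 0.99 | 0.94 | 0.83 | 0.71 |
| 100 | >0.99 | 0.98 | 0.90 | 0.81 |

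With 80 schools, the effect detectable at 90% power is about 3.28 × SE. That is 3.28 × 0.0559 = 0.18 SD at ICC 0.05 and 3.28 × 0.0785 = 0.26 SD at ICC 0.15.

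**Step 4: the cap.** Assume a school ICC of 0.05 plus a class ICC of 0.05, and 20 children per class.
- 50 schools × 2 classes: V = 0.05 + 0.05/2 + 0.90/40 = 0.0975; SE = √(4 × 0.0975 × 0.64/50) = 0.0707; power 0.79.
- 100 schools × 1 class: V = 0.05 + 0.05 + 0.90/20 = 0.145; SE = √(4 × 0.145 × 0.64/100) = 0.0609; power 0.90.

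The number of children is the same (2,000), but power differs by about 0.11.

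**Step 5: if 40 were the total.** With K = 40 and ICC 0.05, SE = √(4 × 0.0975 × 0.64/40) = 0.0790 and power is 0.69.

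**The case against.** A fair defence has five parts.

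- **The power claim may be true.** Under the assumptions above, 80 schools exceed 90% at ICC 0.05 or below, and 100 schools reach 0.90 at ICC 0.10. At ICC 0.02, 80 schools reach 0.92 even without baseline adjustment. If small means 0.30 SD, 80 schools with r = 0.6 keep at least 0.96 up to ICC 0.15. This stands. A reader might infer that the promised power is not delivered, but the documents do not show that.
- **Forty may simply be per arm.** It is exactly 80 / 2. This also stands as a possibility, so calling the phrase impossible goes too far. The wording still needs correcting, because the text does not say per arm.
- **Low power figures need unplanned conditions.** A reader might infer a general power of 40 to 80%. Values near the bottom of that range need 40 schools in total and no baseline adjustment. Section 8 plans an ANCOVA, and 80 to 100 schools with baseline give 0.71 or more over the ICCs examined.
- **The cap may never bite.** It applies only if more than 100 teachers consent, and nothing in the protocol predicts 50 schools with two classes each. That scenario only illustrates what the rule permits. The rule still samples a unit other than the one randomised.
- **The statistical analysis plan is not shown and may hold the inputs.** That is a reason not to call the figure false. It does not repair the class count, the mixed units or the teacher-level cap, which are in the protocol text.

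**Conclusion.** The point holds as a defect in the stated sample size and as an unsupported power claim. It does not show an underpowered trial.

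Two parts rest on the text alone: the 40-class phrase is wrong as a total, and one sample size is expressed in three units that the design does not make equivalent.

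The power part rests on assumed inputs (0.20 SD, two-sided 5%, 20 children per school, r = 0.6, no attrition). On these, 80 schools run from 0.99 at ICC 0.02 to 0.71 at ICC 0.15, so >90% is conditional on an ICC that the sentence does not give. The possible loss from the teacher-level cap, about 0.90 to 0.79 in the illustration, is real but hypothetical.

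**What to change.** 1. State the sample size in schools in the lay abstract, section 4.1, note b to Figure 1 and section 8. Give classes and teachers only as derived numbers.
2. Change the parenthesis in section 8 to 40 schools per arm if that is what was meant. Otherwise delete it.
3. Replace the bare >90% with power, or the effect detectable at 90% power, over a stated range of ICC, children per school and baseline correlation. Give the numerical effect and alpha.
4. If the cap is used, apply it by school: one teacher per school first, and further teachers only if places remain. Section 4.4 schedules recruitment from December 2022 and the intervention to June 2023, so selection may already be complete. In that case report the number of schools obtained and the power for that number.

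The cost is wording, a less favourable conditional power figure, and a minor change in how the cap is drawn if it is still open. No extra schools are needed.

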## **9. Preparatory and follow-up studies**

### **9.1. Evaluation of the quality of mental health and pedagogical activities in the tool kit**

We will recruit 5th and 6th grade teachers to evaluate the quality of 15 wellbeing activities and 14 educational activities involving nature between May and June 2022. These teachers will be recruited via social networks. Approximately 30 teachers will be asked to test 4 activities with their students and answer a short 7-item confidential online questionnaire (i.e., “I would use this activity with another class in the future” using a scale ranging from 1 (strongly disagree) to 5 (strongly agreed)). Teachers will receive a \$25 CAD e-transfer as compensation. Teachers will also be invited to provide suggestions to improve activities using an open response format. Consent will be obtained for all teachers (available on demand).

### **9.2. Pilot**

We will recruit teachers from three to six 6th grade classes by sourcing our network. The teachers will participate in a pilot study that will take place from September to December 2022. Teachers and parents or legal guardians of the students will sign information and consent forms (available in French on demand), but will not be randomized. All participants will receive intervention, i.e., access to activities and supervision. The procedure will take place over a shorter period of time (6 weeks instead of 12 weeks). Teachers will receive a financial compensation of \$100 CAD per questionnaire (\$200 CAD in total) in the form of a gift card. Consent will be obtained for all teachers (available on demand).

**9.3. Feedback survey following RCT**

We will administer an optional, anonymous survey to teachers who participated in the 12-week intervention program as part of the randomized controlled trial. The goal of this survey is to obtain feedback on teachers' experience during their participation in the intervention and will allow us to better assess the feasibility and effectiveness of *Open sky School* in schools. This feedback will also allow us to modify and improve this curriculum in the future, to better meet the needs of teachers and students. In the fall of 2023, participating teachers in the intervention group will be contacted by email and will be invited to complete the optional survey if they wish to provide feedback on their experience. In winter 2024, participating teachers in the control group who choose to participate in the 12-week intervention will also be contacted by email. The survey will be administered through Qualtrics, a secure online platform. Consent will be obtained for all teachers (available on demand).

